## Methods and analysis

### Study design

We will undertake a mixed methods study with five closely linked work packages (WPs). WP1 will take a natural experimental approach to identify the effects of UC on mental health and well-being using two large-scale population surveys, the UK Household Longitudinal Study (UKHLS)^17^ and the Annual Population Survey (APS).^18^ We shall use the information about the phased implementation of UC that is made publicly available via the DWP’s Stat-Xplore system^19^ to define exposed and unexposed groups and compare changes in the health of survey respondents exposed to UC, with changes in the health of respondents living in areas where legacy benefits still apply. We will also use a longitudinal neighbourhood dataset for 42 000 small areas (Lower Layer Super Output (LSOA) areas in England and Wales; Datazones in Scotland), the National Institute for Health Research (NIHR) North West Coast Applied Research Collaboration—Place-based Longitudinal Data Resource.^20^ The dataset includes monthly measures indicating which population groups (eg, new claimants, existing claimants, people with/ without children, people with disabilities) were affected by the phased rollout of UC in each neighbourhood in each time period. To identify any area-level mental health effects of UC, we will use a composite neighbourhood mental health measure—the Small Area Mental Health Index (SAMHI), available annually for the same small areas, but adapted to include Scotland.^21^ Using the COVID-19 waves of the UKHLS, we shall compare mental health among new UC claimants, other respondents who have experienced income losses and existing UC claimants. These analyses will be primarily descriptive rather than designed to formally identify impacts.

WP2 will analyse administrative data collected by CA on the characteristics of people seeking help in connection with UC claims between 2017 and 2020, a survey conducted in the North East of England on financial stress associated with the UC application process in September/October 2019, and a linked dataset derived from the Liverpool ‘advice on prescription’ service, which combines CA data on advice-seeking with information about use of health and social care services.

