### Sample size and statistical power

The UKHLS includes approximately 40 000 households who are surveyed annually. The 2009–2022 survey datasets will include approximately 280 000 observations on around 52 000 adults and 30 000 observations on 5000 children. To identify the impact of UC, we will conduct difference-in-difference (DiD) analyses, comparing members of households newly exposed to UC as rollout proceeds, with households who are unlikely to be exposed. Focusing on child health outcomes, because the numbers available are smaller, in the UKHLS datasets from 2009 to 2018 we will have 300 children in the intervention group and 3300 in the control group, providing 80% power to detect an 8% relative increase in Strengths and Difficulties Questionnaire (SDQ) scores. This is a markedly smaller effect than the 20% relative increase in the prevalence of psychological distress we found in our previous study^4^ of the impact of UC on adult mental health up until 2018, so provides a conservative estimate of the power of the proposed study. The sample size in the UKHLS COVID-19 surveys is approximately 10 000, of whom approximately 4000 reported substantial (>5%) income losses, and around 300 reported new UC claims in the April survey wave. Currently, nine waves of data are available, from April 2020 to September 2021, with questions about UC included in waves 1, 2, 4, 6, 8 and 9.^30^

The APS collects self-assessed health and well-being data on approximately 180 000 working age people per year, so provides good power for England–Scotland comparisons and other subgroup analyses. Our analysis of area level mental health effects will use annual data from a longitudinal dataset of 42 000 neighbourhoods from 2011 to 2022, or approximately 504 000 neighbourhood-years.

The CA survey dataset contains information on approximately 280 000 people who seek advice. The longitudinal survey contains information on 250 people, with a response rate of 85%. The advice on prescription dataset contains information on approximately 5000 people each year since 2014.

For the qualitative study, we will recruit up to 80 UC claimants aged 18–66 (state pension age), divided equally between the 2 study sites. We will seek to reinterview 40 first round respondents 18–24 months after their first interview, a subsample of interviewees using photovoice methods.^22^ We will aim to interview up to 15 staff from a range of organisations in each study site.

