### Analysis plan

To identify the effects of UC in the UKHLS and APS datasets (WP1), we will fit difference-in-differences (DiD) models, with terms for group and period to define respondents who are exposed or unexposed to UC, depending on their sociodemographic characteristics, location and date of interview, and a group by period interaction term to identify the effect of UC. We will add individual and area-level covariates to account for time-varying confounders^36^ and fit mixed-models to account for clustering of observations within households and areas. Sensitivity analyses will be conducted using alternative definitions of exposed and unexposed populations. We will test the validity of the key identifying assumptions, such as common preintervention trends, and use additional (eg, matching) methods if needed. We will also conduct falsification tests using placebo outcomes to test for specificity of effects.

For the SAMHI analyses, we will use fixed-effect panel regression methods to investigate whether increases in UC in each LSOA are associated with changes in mental health problems, while controlling for time-varying confounders (eg, local government expenditure).^37^ We will check the robustness of the results by using alternative ways of estimating effects, such as continuous DiD and synthetic control methods^38^ to compare outcomes in areas where UC has been introduced and areas not yet exposed.

To investigate the extent to which changes in income, employment status and financial housing difficulties (such as rent arears) mediate the effects of the introduction of UC on health outcomes, we will undertake causal mediation analysis adjusting for time-varying confounding.^39–41^ Subgroup analysis will investigate differences in health impacts between Scotland and the rest of Great Britain (GB), or between areas with differing labour market characteristics. By stratifying the analysis before, during and after the pandemic we will investigate whether moving onto UC had the same effect during these different time periods, when the policy and wider social context were very different. Using the COVID-19 waves of the UKHLS, we shall compare mental well-being among new UC claimants, other respondents who have experienced income losses and existing UC claimants. These analyses will be primarily descriptive rather than designed to formally identify impacts.

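### Clustering named only for households and areas does not cover area-by-time shocks, so intervals for the UC effect may be too narrow, especially in the APS

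*Protocol article*

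**What the plan says.** Under Analysis plan, the WP1 effect in UKHLS and APS is estimated with "a group by period interaction term to identify the effect of UC". Respondents are classed as exposed or unexposed "depending on their sociodemographic characteristics, location and date of interview". Dependence is handled by a plan to "fit mixed-models to account for clustering of observations within households and areas". For these two surveys the article names no person level, area-by-period term, serial-correlation structure or cluster-robust variance, and it does not define the areas. Fixed-effect panel regression is named only for the separate neighbourhood (SAMHI) analysis.

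Under Study design, changes in exposed respondents are compared with "changes in the health of respondents living in areas where legacy benefits still apply". Under Sample size and statistical power, the comparison is with households unlikely to be exposed, which need not live in other areas.

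The same section gives the data volumes: UKHLS has "approximately 280 000 observations on around 52 000 adults and 30 000 observations on 5000 children", and the APS covers "approximately 180 000 working age people per year".

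**The concern.** Rollout switches exposure on in particular places at particular dates. Suppose a local event, such as a plant closure or a cut to a local service, shifts mental health for everyone in an area for a while. That shift is then an error shared by many respondents at the level where exposure changes. A random intercept for area is constant over time and cannot represent it. The model then counts residents of the same area and period as more independent than they are.

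The safeguards listed in the Analysis plan (pre-trend tests, placebo outcomes, alternative exposure definitions, matching) address bias. They do not correct a standard error.

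The group-by-period term is the study's main causal estimate. WP4 takes effects from the other work packages and builds its credible intervals from the uncertainty in sample-based parameters. WP5 uses the WP1 estimates directly. An understated standard error would carry into both.

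**Working it through.** The article states no intraclass correlation, design effect or standard error for these models, so there is no plan figure to reproduce on this point. The only power figure (80% for children's SDQ scores) comes without a mean, SD or correlation and cannot be checked. All variance components below are assumptions, shown as ranges.

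**1. Repeated measures (from Sample size and statistical power).** 280 000 / 52 000 = 5.4 observations per adult; 30 000 / 5000 = 6 per child. With "approximately 40 000 households who are surveyed annually", 52 000 / 40 000 is about 1.3 adults per household. This is rough, because the two counts have different bases.

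**2. Area-by-period variance ignored.** Take cell means with *m* people per area-period cell, area-by-period variance τ² and residual variance σ² = 0.98, in a two-way difference-in-differences (150 areas, 12 periods, staggered start). With shocks independent over time:

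R = model SE / true SE = 1 / √(1 + m τ² / σ²); coverage of a nominal 95% interval = 2Φ(1.96 R) − 1.

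| m | τ² = 0.001 | τ² = 0.005 | τ² = 0.02 |
|---|---|---|---|
| 20 | 0.99 | 0.95 | 0.84 |
| 100 | 0.95 | 0.81 | 0.57 |
| 500 | 0.81 | 0.53 | 0.30 |

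For example, at m = 500 and τ² = 0.005: 1 / √(1 + 2.5 / 0.98) = 1 / √3.551 = 0.53. Coverage in the τ² = 0.005 column is 93.8%, 88.9% and 70.2%. The worst cell (R = 0.30) covers 44%. Shocks with autocorrelation 0.8 gave similar ratios at τ² = 0.005: 0.96, 0.84 and 0.57.

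**3. Where the APS might fall.** If there were 370 areas (assumed), 180 000 / 370 = 486 people per area-year. If only 5% to 30% belong to relevant groups (assumed), cells hold about 24 to 146. At τ² = 0.005:

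- m = 24: 1 / √1.122 = 0.94
- m = 146: 1 / √1.745 = 0.76
- m = 486: 1 / √3.480 = 0.54

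UKHLS child cells would be far smaller: 30 000 / (370 × 14 years) is about 6.

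**4. UKHLS-like panel.** This uses 60 areas, about 20 people each and 8 waves, with total variance about 1 (area 0.02, household 0.10, person 0.40). The ratio for a household + area model, with residuals independent over time, was:

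| Setting | 1 adult per household | 1.3 | 2 |
|---|---|---|---|
| Person level omitted, no area-by-period variance | 1.00 | 1.08–1.09 | 1.19 |
| Area-by-period variance 0.02 also omitted, all residents exposed | 0.75 | 0.82 | 0.90 |
| Same, but 30% of households eligible and same-area ineligible residents as controls | 0.90 | 0.97 | 1.06 |

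Coverage in the second row is 86%, 89% and 92%. The first row shows that leaving out the person level makes a within-person interval correct or too wide. The third shows that local shocks largely cancel when controls share the area.

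**5. A person intercept alone is not enough.** With person residuals autocorrelated at 0.5 and no area-by-period variance, a person + household + area model had a ratio of 0.90. With 1.3 adults per household, 30% eligible and area-by-period variance 0.02, adding the person level moved the ratio from 0.97 to 0.90, because it removed an offsetting excess width.

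**6. Clustered variance.** In a separate simulation (370 areas, 10 years, staggered exposure, 1500 runs per setting), area-clustered standard errors gave type I error of 4% to 6% in nearly all settings.

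**The case against.** The sentence does not say that households and areas are the only levels, and it does not exclude a robust variance. This is a condensed article, and the full random-effects structure could sit in an analysis plan that is not shown. That stands as a caution about wording. It does not dispose of the point, because the article states which clustering the models are meant to handle, and those levels do not match how exposure varies.

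A reader might infer that both gaps, person and area-by-period, push intervals in the same direction, so that they are usually too narrow and the false-positive rate exceeds 5%. The documents do not support this. The person-level gap works the other way or not at all, and the net ratio in the UKHLS-like settings ran from 0.75 to 1.19. With about 1.3 adults per household, the household intercept already carries much of the person effect, so it would also be too strong to say that the within-person comparison is lost.

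A reader might also take UC as assigned purely by area and period. The Analysis plan adds sociodemographic group, so some controls may live alongside the exposed. It also plans area-level covariates for time-varying confounding, which may absorb part of a local shock. Both reduce the problem; neither is shown to remove it. The contrast in Study design is with areas still on legacy benefits, where shocks do not cancel.

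Finally, the most alarming ratios need cells close to the whole APS working-age sample. Claimant-type subgroups would be smaller, as step 3 shows.

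**Conclusion.** The point holds as a risk. The stated clustering does not cover area-by-time shocks or serial correlation, so intervals for the group-by-period effect may be too narrow. The exposure is greatest in the APS and where controls come from other areas. Illustratively, at area-by-period variance 0.005 the ratio of model to true standard error falls from 0.95 (20 per cell) to 0.53 (500 per cell). It is closer to 1 with same-area controls and close to 1 in very small cells, such as those for children.

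These sizes rest on assumed variance components, cell sizes, numbers of areas and control groups, none of which the article gives. A specific error rate, or the statement that the intervals are wrong, would go beyond the evidence.

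**What to change.** Keep the models and amend the clustering clause. Report standard errors clustered at the geographic unit by which UC was rolled out, name that unit, and apply this in both the UKHLS and APS analyses. Add a person effect in UKHLS alongside the household effect. The two changes belong together, since a person effect without clustered variance can leave intervals too short (step 5).

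An area-by-period random effect alone is not an equivalent substitute. If independent between periods, it does not represent local shocks that persist, and it was not tested against such shocks. Clustering by area allows for that persistence, and for serial correlation in people who stay in the area.

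The cost is a sentence in the plan and a standard software option. The downside is that intervals will probably be somewhat wider.

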To date, the evidence of health impacts relates to a period when UC had only been implemented for some groups of new claimants. The overall health and equity impacts may change markedly as legacy benefit recipients migrate to UC. Substantial but temporary changes in the way UC is administered were made in response to the economic shock associated with the COVID-19 lockdown measures in early 2020. Conditionality and some forms of debt recovery were suspended for 3 months and have since remained well below prepandemic levels. The standard cash allowance (the most a household could receive, before taking income and savings into account) was raised by £1000 per annum from April 2020 until October 2021^14^ A very large number of new claims were made and processed in the early months of the lockdown. Claims rose 9-fold, to 500 000 per week in early April 2020, and the caseload doubled from 3 to 6 million, before new claims returned to previous levels by July 2020.^15^ A new cohort of UC recipients has been created whose composition is likely to differ significantly from the pre-COVID-19 caseload (eg, they are less likely to have received benefits in the past and more likely to have savings).^16^ As well as estimating the impact of UC on population mental health, we shall explore the experiences of these new recipients to gain insights into whether differences in health impacts might be expected.

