Our objectives are: (1) to measure the impacts on mental health and well-being among adults and children affected by UC, compared with a legacy-benefits comparator group; to explore how impacts are distributed and effects vary between England/Wales and Scotland, and the implications of the COVID-19-related changes to UC for the health of recipients; (2) to identify features of the UC claim and payments process associated with health difficulties for claimants, and to explore inequalities within and between regions in the pattern of advice-seeking from Citizens Advice (CA); (3) to explore the ways in which the experience of claiming and managing UC affects claimants’ health, and how experiences differ between England/Wales and Scotland; (4) to develop a microsimulation model to investigate possible income, employment and health consequences of differing UC implementation scenarios, up to 10 years post implementation; (5) to measure the cost–consequence of UC, analyse its distributional consequences and conduct cost–benefit analyses of moderating/mitigating measures implemented in Scotland or by specific local authorities.

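### Comparing period-stratified estimates to judge whether UC had the same effect before, during and after the pandemic can mistake a change in who is exposed for a change in effect

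*Protocol article*

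**What the plan says.** The Analysis plan for work package 1 fits DiD models to the two surveys and then sets out the pandemic question: "By stratifying the analysis before, during and after the pandemic we will investigate whether moving onto UC had the same effect". The method is therefore stratification by period. Policy and social context are the only things named as differing between the strata.

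The Introduction describes a third difference: "A new cohort of UC recipients has been created whose composition is likely to differ significantly from the pre-COVID-19 caseload". It gives examples: "they are less likely to have received benefits in the past and more likely to have savings". The scale was large. On new claims: "Claims rose 9-fold" at the April 2020 peak. On the stock: "the caseload doubled from 3 to 6 million".

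The Intervention section expects effects on health to vary, with some households better off and others worse off. The first objective includes "the implications of the COVID-19-related changes to UC for the health of recipients".

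The models carry individual and area covariates for time-varying confounding. Matching is available if the identifying assumptions call for it. Sensitivity analyses vary the definition of exposed and unexposed. The named subgroups are Scotland against the rest of Great Britain and areas with different labour markets. The comparison of new and existing claimants in the COVID-19 survey waves is labelled as mainly descriptive.

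**The concern.** A DiD estimate within one period averages the effect over the people exposed in that period. Three such estimates answer whether the effect was the same only if the three exposed groups are alike in whatever modifies the effect, or if nothing modifies it. The article gives reason to doubt both: it says that the recipients changed and it expects effects to differ between households.

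Covariates entered as main effects adjust outcome levels between exposed and unexposed people within a period. They do not align effect modifiers between periods. None of the other steps listed in the Analysis plan does so either.

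At stake is the first objective. A smaller estimate during the pandemic could be taken as a sign that the temporary changes to UC protected mental health, when it may show only that a different set of people was exposed.

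**Working it through.** The plan gives no figure for this comparison, so there is none to reproduce. The check asks whether a change in mix alone can move the period estimates, and whether covariates prevent it.

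**Inputs from the article**
- Stock of claimants: 3 to 6 million. If every earlier claimant stayed (an assumption), 3/6 = 50% of the later stock is new.
- Flow of claims: 9-fold at peak, so up to 8/9 of peak claims were above the usual flow.
- Earlier estimate: a 7-percentage-point rise in psychological distress among unemployed people in UC areas.

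**Assumed inputs.** The article gives neither the effects by claimant type nor the first-time shares. All values below are illustrative.

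**Formula.** Let a be the effect in claimants with a benefit history, b the effect in first-time claimants, and p the first-time share, with a and b the same in every period. Then:

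- period average = a(1 − p) + bp
- change between periods = (b − a)(p₁ − p₀)

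| a | b | p₀ to p₁ | Average before | Average during | Change |
|---|---|---|---|---|---|
| 7 | 0 | 30% to 60% | 7 × 0.70 = 4.9 | 7 × 0.40 = 2.8 | −2.1 (43%) |
| 7 | 0 | 20% to 60% | 7 × 0.80 = 5.6 | 7 × 0.40 = 2.8 | −2.8 (50%) |
| 7 | 3 | 30% to 50% | 4.9 + 0.9 = 5.8 | 3.5 + 1.5 = 5.0 | −0.8 (14%) |
| 7 | 7 | any | 7.0 | 7.0 | 0 |

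The change is zero when a = b or when the share does not move. Its sign follows b − a, so if first-time claimants were harmed more, UC would look worse during the pandemic.

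The 7 points is not a type-specific effect. It is an average in one group, and using it for a puts the pre-pandemic average below 7. The proportional result does not depend on that choice. With b = 0 the relative fall is 1 − (1 − p₁)/(1 − p₀), which for 30% to 60% is 1 − 0.40/0.70 = 43% whatever the value of a.

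**Do covariates remove it?** A simulation used 400,000 observations per stratum, constant effects of 7 and 0, and claimant type entered as a main effect in each stratum's DiD model. The share with a benefit history was set to 0.90, 0.50 or 1/9.

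| Share with benefit history | Expected average | Covariate-adjusted DiD | Standardised to the 0.90 mix |
|---|---|---|---|
| 0.90 | 7 × 0.90 = 6.30 | 6.25 | 6.25 |
| 0.50 | 7 × 0.50 = 3.50 | 3.39 | 6.17 |
| 1/9 | 7 × 1/9 = 0.78 | 0.82 | 6.43 |

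The covariate-adjusted estimates follow the mix. The standardised estimates stay level apart from simulation noise.

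**The case against.** The strongest reply is that this is one sentence in a condensed article, and a full analysis plan may standardise the comparison. That is possible, and the article does not rule it out. But it does fix stratification by period as the way to answer the question, and it frames the periods by policy and context alone. An added comparison is therefore a change of method rather than a missing detail.

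Other replies stand and limit the point:

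- **No rule of attribution.** The article does not say that a difference will be credited to policy or context. Each estimate can be a sound average for its own period.
- **The change is recognised.** New and existing claimants are compared descriptively, work package 2 profiles advice-seekers, and work package 3 compares longer-term and later claimants. The strengths box says that such information will inform the quantitative design. This makes a naive reading less likely but does not standardise the comparison.
- **Effect modification by the shifted traits is not established.** The Intervention section points to tenure, disability, self-employment and lone parenthood, not to savings or benefit history. The Introduction treats different impacts in the new cohort as an open question.
- **The caseload is not the exposed group.** Exposure is defined by sociodemographic characteristics, location and interview date, so the exposed group's mix need not have moved as far as the caseload's.

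A reader might also infer that the work package 4 scenario for early-pandemic UC inherits the problem. The article does not say that period-specific estimates feed that scenario, so this is not supported.

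**Conclusion.** The point holds in conditional form. Comparing period-stratified DiD estimates can show a change in UC's effect that comes only from a change in who is exposed, and the stated covariates would not correct it. It requires that effects differ by the characteristics that shifted. The article makes this plausible but does not show it.

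The size is unknown. The illustrations run from no change to a fall of 2.8 points (50%) in the first table, and to larger falls under the extreme mix in the simulation. All rest on assumed effects and shares, and the direction is not known either.

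Two stronger readings go too far. One is that a mix shift will certainly be read as a change in what UC does: the article supports only that it can be. The other is that whatever difference remains after standardisation measures policy or context. Unmeasured differences between recipients may remain. So may changes in the comparator, since the Intervention section says that rollout to new unemployed claimants was complete by December 2018.

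This is a worthwhile and inexpensive improvement. It does not invalidate the period estimates themselves.

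**What to change.** In the Analysis plan, at the sentence on stratifying by pandemic period:

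1. Keep the crude between-period comparison and label it as such.
2. Add a comparison standardised to the pre-pandemic mix of the exposed group, by reweighting the later strata or by exposure-by-characteristic terms averaged over that mix.
3. Use only pre-exposure characteristics that each survey actually holds, for example household type, earlier benefit receipt and employment, and previous-wave mental health in the UKHLS. The article does not show that savings or work history are available, so list the set for each survey.
4. Restrict the standardised comparison to the region of overlap, and report who falls outside it.
5. Do not read the crude difference as an effect of changed policy or context. Base that reading on the standardised difference, and state that unmeasured differences in recipients and changes in the comparator may remain.

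The cost is a change of wording and one further analysis of the same surveys. Intervals will be somewhat wider, which matters because the strengths box already warns that fixed sample sizes limit subgroup work. Claimant types that were rare before 2020 drop out of the standardised comparison and can be described only for their own period.

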### Sample selection

In WP1 we will analyse data on people of working age and their children from 2009 to 2022 in the UKHLS, and on people of working age from 2011 to 2024 in the APS. The UKHLS and APS use stratified clustered random probability samples of the UK population. The CA surveys (WP2) include adults in England who have contacted CA for assistance with claiming UC from 2017 onwards. For a subsample of respondents from North East England, a survey conducted by CA was in August 2019 and a follow-up questionnaire was administered in October 2019 to all individuals who had made a UC claim to understand the characteristics of people who experience financial hardship. The ‘advice on prescription service’ data is available for people engaging with CA Liverpool from 2014, but linked data will span 2010 to 2023.

The samples of UC claimants for WP3 will be drawn from two large urban areas, Tyne and Wear (population 1.1 million) in North East England and the Glasgow City Region (population 1.2 million) in Scotland. A number of recruitment strategies will be used, including via gatekeepers^8 9^ in public, voluntary and community sector organisations, workplaces and trades unions, and via social media and leaflets placed in community locations such as libraries. We will aim for a maximum variation sample, taking account of age, gender, ethnicity, household composition, education level, health, disability, employment and housing status. The sample will include people who have been on UC for some time, new claimants and those transferring to UC from legacy benefits. We will include people who were claiming UC prior to March 2020, people who claimed UC during the UK’s lockdown period and those who have become claimants later due to the economic impact of the pandemic. We will recruit staff from a range of organisations in each locality via our extensive professional networks in each conurbation.

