In WP2, we will carry out descriptive analyses of the England-wide CA survey data to summarise the health and sociodemographic characteristics of people seeking advice in applying for UC, and explore differences at the local authority level in key demographic and health characteristics of advice seekers. We will use the longitudinal CA dataset to describe the sociodemographic and health characteristics of people who are most and least likely to experience financial insecurity as a result of the 5-week wait for the first payment. We will also apply longitudinal multivariable regression to the advice on prescription linked dataset, similar to the methods used in WP1. We will use the cross-sectional national data from March 2020 onwards to explore changes in the sociodemographic and health profile of people seeking advice with UC claims following the COVID-19 pandemic.

In WP3, we will apply thematic content analysis to the longitudinal qualitative data,^42^ using NVivo software to assist data management, retrieval and sharing between members of the research team. A comparative analysis across time, locality and participant characteristics will be undertaken to identify possible pathways linking the experience of claiming UC with health outcomes, and how they vary between claimants and between study sites. This will enable identification of differences of experience by locality and in-depth analysis of characteristics including gender, age and employment status, as well as facilitating comparisons of the experiences of longer term (pre-COVID) and post-COVID claimants. Photovoice data will be coded and incorporated within the analysis of the interview material.^22^ Interviews with staff will also be analysed thematically.

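### Half of objective 2 concerns inequalities in advice-seeking, but the national WP2 analysis describes only the make-up of advice seekers, which does not identify them

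*Protocol article*

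**What the plan says.** Objective 2, at the end of the Introduction, has two halves. The first is "to identify features of the UC claim and payments process associated with health difficulties for claimants". The second is "to explore inequalities within and between regions in the pattern of advice-seeking from Citizens Advice".

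Under Sample selection, the CA surveys "include adults in England who have contacted CA for assistance with claiming UC from 2017 onwards". Under Sample size and statistical power: "The CA survey dataset contains information on approximately 280 000 people who seek advice". No count of UC claimants stands beside that figure.

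For the England-wide data, the Analysis plan sets out descriptive work of three kinds: a summary of the health and sociodemographic characteristics of advice seekers; a comparison between areas, to "explore differences at the local authority level in key demographic and health characteristics of advice seekers"; and, from March 2020, a comparison over time, "to explore changes in the sociodemographic and health profile of people seeking advice with UC claims following the COVID-19 pandemic". It mentions no rate per claimant and no standardisation to the caseload. The health measure named for the CA surveys under Outcomes is a self-reported long-term mental health condition.

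The Introduction also reports that early in the pandemic "the caseload doubled from 3 to 6 million", and expects the new recipients to differ in composition from those before them.

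**The concern.** Inequality in advice-seeking is about who seeks advice among those who could. The national CA data hold the people who did and none of the claimants who did not. A profile of advice seekers mixes two things: the make-up of claimants in that area or period, and each group's propensity to seek advice. Two authorities can show different profiles although every group seeks advice at the same rate in both. They can also show the same profile although propensities differ widely.

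The comparison over time has the same weakness, and here the document supplies the likely confounder: a doubled caseload of different composition. If the plan is followed exactly, its results could create or hide an inequality, and a reader could not tell which. The results also travel. The strengths and limitations box says that information about people seeking advice will inform the design of the quantitative analyses, and the WP5 plan says that findings from WPs 1–3 will inform the choice of consequences.

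**Working it through.** The plan states no rate, sample size or power for this analysis, so there is no figure to reproduce. The check asks what a profile can and cannot show.

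**Input from the document.** The caseload goes from 3 to 6 million (Introduction).

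**Assumed inputs; the document gives none of these.** The share p of claimants with a mental health condition is 30% or 40% in the old caseload and 10% to 30% in the added 3 million. The rate ratio RR of advice-seeking (condition v none) is 1 to 3 and does not change over time.

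**Formula.** Share of advice seekers with the condition: s = p·RR / (p·RR + 1 − p). After doubling, p is the mean of the old and added shares, because each contributes 3 million.

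**1. Comparison over time, propensities constant**

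| RR | Old p | Added p | New p | s before | s after | Change (points) |
|---|---|---|---|---|---|---|
| 1 | 40% | 30% | 35% | 40.0% | 35.0% | −5.0 |
| 2 | 40% | 30% | 35% | 57.1% | 51.9% | −5.3 |
| 2 | 30% | 10% | 20% | 46.2% | 33.3% | −12.8 |
| 3 | 40% | 30% | 35% | 66.7% | 61.8% | −4.9 |
| 3 | 30% | 10% | 20% | 56.2% | 42.9% | −13.4 |
| 2 | 40% | 40% | 40% | 57.1% | 57.1% | 0 |

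Example, third row: before, 0.30×2 / (0.30×2 + 0.70) = 0.60/1.30 = 46.2%; after, 0.20×2 / (0.20×2 + 0.80) = 0.40/1.20 = 33.3%. The fall is about 5 to 13 points when the added claimants differ in mix, and zero when they do not. Over the same grid the number of advice seekers rises 1.75- to 2.0-fold.

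**2. Areas: profiles differ, propensities do not.** With RR = 2 in both authorities, p = 20% gives s = 0.40/1.20 = 33%, and p = 40% gives s = 0.80/1.40 = 57%.

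**3. Areas: profiles agree, propensities do not.** Inverting the formula, RR = (s/p) / ((1 − s)/(1 − p)). With s = 50% everywhere, RR is 4.0, 2.33, 1.5 or 1.0 when p is 20%, 30%, 40% or 50%. One and the same profile fits anything from a fourfold difference to none.

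**4. What a denominator adds.** For the third row of the table: before, (0.4615/0.30) / (0.5385/0.70) = 2.0; after, (0.3333/0.20) / (0.6667/0.80) = 2.0. Once p is known, the unchanged propensity is recovered although the profile moved by 12.8 points.

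**The case against.** **The analyses are descriptive.** The Analysis plan says so and speaks of exploring profiles. A reader might infer that WP2 will present caseload shifts as changes in need for advice. The text does not support that: it mentions neither need nor propensity, and the Introduction reports the caseload change openly. A changed profile remains a true description of who seeks advice. This stands, so the point is a risk of misreading and not a stated wrong inference. It does not remove the mismatch, because even a descriptive answer about inequality in advice-seeking needs the population at risk.

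**Objective 2 is wider than this.** A reader might also infer that WP2 cannot answer objective 2 at all. That goes too far. The first half needs no advice-seeking rate, the 5-week-wait survey and the linked Liverpool data are separate analyses, and the Abstract frames WP2 largely as a description of advice seekers. The word pattern in the second half can be read loosely, and local profiles are a partial answer. Only the second half of the objective, set against the national analysis, is at issue.

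**The article is condensed.** Denominators may be in a fuller plan, and nothing excludes them. That is fair for detail such as table layout. Here, though, the article states the measure to be compared, and that measure is composition.

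**The illustration sizes nothing in this study.** All prevalences and rate ratios are assumed. It uses the stock of claimants, whereas the data concern help with making a claim, so new claims fit better; the Introduction says these were back at previous levels by July 2020. A lasting shift is therefore not shown. This stands in full.

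**The denominators are unproven.** Stat-Xplore is cited for the phasing of implementation. The document does not show that it holds counts by age, sex or mental health condition, or that the Annual Population Survey (APS) has a matching condition measure. This stands and limits the fix.

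**Conclusion.** The point holds in a limited form. The second half of objective 2 is not matched by the national WP2 analysis, which describes only the composition of advice seekers by local authority and following the pandemic. Composition alone does not identify inequality in advice-seeking, and the comparison over time risks confounding by the caseload change that the document itself describes.

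The size cannot be derived from the documents. The range of roughly 5 to 13 percentage points for the comparison over time rests on the assumed prevalences, on rate ratios of 1 to 3 held constant, and on the caseload stock. It is zero if the claimant mix did not change. No figure in the document is shown to be wrong. The change should be made because the objective and the stated measure differ and the remedy costs little.

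**What to change.** In the WP2 part of the Analysis plan, add UC advice contacts per new UC claim (or per person on UC) by local authority and period. Take denominators from the area-level UC claimant data that WP1 already uses, and standardise by whatever characteristics those counts carry. Keep the profile tables as description.

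For mental health condition, report a rate only if a matching claimant or survey denominator is available. Otherwise present the profile with an explicit statement that it reflects claimant mix as well as advice-seeking, and narrow objective 2, for that characteristic, to the profile of advice seekers.

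The cost is a little extra analysis and no new data collection from participants. The downside is that denominators may exist for some characteristics only, so part of the objective may have to stay descriptive.
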